### Secondary Outcome Measures

The secondary outcomes include social network size, psychological well-being, life satisfaction, stress level, sleep quality, symptoms of depression and anxiety, physical health, and cognitive health.

**Social network size.** Social network size is assessed using the Chinese validated Lubben Social Network Scale (57,63). The Lubben Social Network Scale consists of two sets of three questions. The first set evaluates the kinship ties of participants: “How many relatives do you see or hear from at least once a month?”; “How many relatives do you feel close to, such that you could call them for help?”; and “How many relatives do you feel at ease with that you can talk about private matters?” The second set evaluates the non-kin ties of participants by asking three parallel questions. The only difference is that the word *relatives* is replaced with the word *friends*. Participants indicate the number of social partners on a 6-point scale (0 = none to 5 = more than 9 people), deriving in sum scores representing larger network sizes for a total of relatives/friends as well as for friends and family separately.

**Psychological Well-being.** Participants' psychological well-being is assessed using the Psychological Well-being Scale, originally developed by Ryff and colleagues (64). In this study, we utilize the validated brief version of the scale specifically tailored for the Hong Kong Chinese population, as validated by Chan, Chan, and Sun in 2017 (65). The scale consists of six dimensions of psychological functioning including autonomy (e.g., “have confidence in one’s opinions”), environmental mastery (e.g., “No difficulty in arranging life”), personal growth (e.g., “Have developed a lot as a person”), positive relations with others (e.g., “Enjoy conversations with friends”), purpose in life (e.g., “Enjoy making plans for the future”), and self-acceptance (e.g., “Feel good about self”). Participants will be asked to rate to what extent they agree with each of the statement on a 6-point scale (1 = strongly disagree to 6 = strongly agree).

## Supplement 1. Study Protocol

**Life Satisfaction.** The Satisfaction with Life Scale, originally developed by Diener et al. (66) and validated in Chinese by Sachs (67), is utilized to assess participants' life satisfaction. Participants will be requested to indicate their agreement level with each of the five statements on a 7-point scale, ranging from 1 (strongly disagree) to 7 (strongly agree).

**Stress Level.** Stress level is measured using the 14-item Perceived Stress Scale in its validated Chinese translation (68,69). Participants indicate how often they have experienced the feelings described in the statements in the past month on a 5-point scale (0 = never to 4 = very often). Sample items include “In the last month, how often have you been upset because of something that happened unexpectedly?”; “In the last month, how often have you felt confident about your ability to handle your personal problems?”; and “In the last month, how often have you been able to control irritations in your life?”. As five items are reversed scored, they will be recoded before computing a mean score, with higher scores representing more stress.

**Sleep Quality.** Sleep quality is measured using the Chinese version of the eight-item Sleep Condition Indicator (70,71). Participants are asked to report their sleep quality and continuity, duration and frequency of insomnia symptoms, satisfaction with sleep, and frequency of sleep during the day on a 5-point scale from 0 to 4, with a higher score indicating better sleep quality. Mean scores will be calculated, with a higher score indicating better sleep quality.

**Depressive Symptoms.** Depressive symptoms are assessed using the nine-item Patient Health Questionnaire-9 in its validated Chinese version (PHQ-9) (72, 73). Participants are asked to report the frequency of cognitive, physical, and affective symptoms of depression in the past 2 weeks on a 4-point scale (0 = not at all to 4 = nearly every day). Sample items include “having little interest or pleasure in doing things,” “feeling tired or having low energy,” and “feeling down, depressed, or hopeless.” Means and standard deviations of the items will be used in data analysis, with a higher score indicating a higher level of depression.

**Symptoms of Anxiety and Depression.** The seven-item Hospital Anxiety and Depression Scale (HADS) is used to measure symptoms of anxiety and depression (Anxiety) (74). We adopted the Chinese validated version in Hong Kong (75). Participants indicate the intensity of each symptom on a 4-point scale (1 = not at all, 2 = several days, 3 = more than half the days, and 4 = nearly every day). Sample items include “feeling nervous, anxious, or on edge,” “not being able to stop or control worrying,” and “having trouble relaxing.” Means of the items will be used in data analysis, with a higher score indicating higher levels of anxiety and depression.

**Physical Health.** The physical health of older adults is assessed in four ways. First, self-rated health is measured by asking participants to rate their perceived general health, vision, and hearing status on a 5-point scale (1 = excellent to 5 = bad) (76). Reversed scores will be used in data analysis, with a higher score indicating better physical health.

Second, functional health is measured using the Chinese version of the WHO Disability Assessment Schedule 2.0 (WHODAS 2.0) (77,78). The WHODAS 2.0 consists of 36 items covering six domains (i.e.,

## Supplement 1. Study Protocol

cognition, mobility, self-care, getting along, life activities, and participation). For each item, the participants are asked to rate their level of difficulty over the past 30 days in the domains of cognition (e.g., “Concentrating on doing something for 10 minutes”), mobility (e.g., “Standing for long periods such as 30 minutes”), self-care (e.g., “Washing your whole body”), getting along (e.g., “Dealing with people you do not know”), and life activities (e.g., “Taking care of your household responsibilities”). They are asked to rate the level of difficulty of activities in the domain of participation (e.g., “participating in community activities”) on a 5-point scale (0 = none, 4 = extremely). Sum scores of each category will be used in data analysis, with a higher score indicating a greater level of difficulty.

In addition, chronic diseases are measured by asking participants to complete a list of 22 diseases using 1 for “yes” or 0 for “no” (79). Total score of the chronic diseases will be calculated.

**Cognitive Health.** The Hong Kong version of the Montreal Cognitive Assessment (MoCA) (80,81) is used to assess cognitive health. The MoCA has a possible total score of 30. To facilitate assessment over the phone, the full version of the MoCA is used at baseline, 6-month and 12-month follow-up, and the MoCA 5-minute protocol is used at the 4-week and 3-month follow-up assessments. The full version of the MoCA covers seven cognitive domains: executive functions, naming, attention, language, abstraction, delayed recall, and orientation. The MoCA 5-min protocol consists of four subtests covering five cognitive domains: attention, executive functions, language, orientation, and memory (81). Total scores will be used in data analysis, with a higher score indicating a greater level of cognitive performance.

### Mediators

**Mindfulness.** Mindfulness is measured using the Five Facet Mindfulness Questionnaire in its Chinese version (FFMQ) (82, 83). The FFMQ measures an individual’s general tendency to be mindful in their daily life. The scale contains 20 items covering five facets of mindfulness: observing, describing, acting with awareness, nonjudging of inner experience, and nonreactivity to inner experience. Participants are asked to rate to what extent the statements describe their thoughts and feeling on a 5-point scale (1 = never to 5 = always). Sample items include “I notice the smells and aromas of things (Observing),” “I am good at finding words to describe my feelings (Describing),” and “I perceive my feelings and emotions without having to react to them (Nonreactivity to inner experience). Means will be used in data analysis, with a higher score indicating a greater level of mindfulness.

**Meaningful/Happy Events.** Participants are asked to report up to three of the happiest and/or meaningful events in daily life over the past week. They first select the category of the event on a list of six options (i.e., interpersonal, recreation, spiritual, daily responsibility, learning, and other). They are then asked to rate the levels of happiness and meaningfulness of the event on a 5-point scale (1 = very low to 5 = very high). Means and standard deviations will be used in data analysis, with a higher score indicating a greater level of happiness or meaningfulness.

## Supplement 1. Study Protocol

**Biomarkers.** One third of participants in the sample will be invited to provide saliva samples. After providing detailed guidelines in saliva sample collection, three saliva samples are collected by the participants using Salivette tubes at the participants' homes on 2 consecutive weekdays, three times each day: after waking up, before lunch, and before bedtime, 4 time points (baseline, 4-week, 3-month and 6-month follow-up). Standard instruction procedures and a telephone reminder are provided to participants. The collected Salivette tubes are kept frozen, and the cortisol levels are determined according to the manufacturer's standard using an ELISA kit (Salimetrics, PA, USA). Each participant's diurnal cortisol pattern is identified using four indicators: (1) morning cortisol, (2) evening cortisol, (3) mean cortisol, and (4) the diurnal cortisol slope. Salivary samples are also tested for CRP using the Salivary C-Reactive Protein ELISA kit according to the manufacturer's recommended protocol (Salimetrics, PA, USA).

**Genotyping.** DNA is collected from saliva samples at baseline, and the Infinium OmniZhongHua-8 v1.3 BeadChip with 887,270 SNPs are used, as this type of chip has been widely used for genotyping in Chinese populations. This type of chip is designed to pay particular attention to alleles found in Chinese populations and is the best choice in terms of study design and cost. It covers common, intermediate, and rare variants found in Chinese populations for genome-wide association studies (GWAS). According to the manufacturer's information, it covers 77% of common variants (minor allele frequency [MAF] > 5%), 73% of intermediate variants (MAF > 2.5%), and 65% of rare variants (MAF > 1%) in Chinese populations at  $r^2 \geq 0.8$ . The assay has exceptionally high data quality in terms of call rates (average > 99%), reproducibility (> 99.9%), and low sample repeat rates, and has high signal-to-noise ratios and low overall noise levels, enabling accurate and reliable calls and copy number analysis. The Sequenom platform is used in the second stage of variant genotyping. The Sequenom system is based on single-base extension (SBE) chemistry and mass spectroscopy, and allows SNPs to be designed for 40-plex assays. If it is necessary to sequence candidate genes, mutation screening is conducted by direct sequencing of exons, intron-exon boundaries, and conserved promoter elements using the ABI 3730XL sequencer in the CGS HKU genotyping core facility. Thus, candidate genes, GWAS, polygenic risk scores, and SNPs from underlying biological pathways are used as genetic dispositions.

### Process Evaluation

To ensure the quality of and satisfaction with Tele-BA, Tele-MF, or Tele-BF intervention sessions, participants will be asked to complete the Treatment Evaluation Inventory (TEI) (84) and two additional questions about their volunteer's delivery of interventions at their 4-week follow-up assessment.

The 11-item TEI is forward-translated into Chinese and backward-translated according to Brislin (1980) (85) and then adapted to the context of interventions on reducing loneliness. Participants will be asked to rate the acceptability (e.g., "I find this treatment to be an acceptable way of dealing with loneliness"), appropriateness (e.g., "I find this treatment to be an appropriate way of dealing with loneliness"), and predicted effectiveness (e.g., "I believe this treatment is likely to be effective") of the interventions they received on a 7-

## Supplement 1. Study Protocol

point scale (1 = not at all to 7 = very much). The mean of the items will be used in data analysis, with higher scores indicating more favorable evaluation.

In addition to questions about the intervention, participants will be asked to rate their satisfaction with their volunteer. They will be asked to rate the extent to which they perceive their volunteer as an effective interventionist on a 7-point scale (1 = not at all to 7 = very much). Means will be used in data analysis, with a higher score indicating greater satisfaction.

### Demographic Information

In addition, the following sociodemographic information is collected as potential covariates: (1) age; (2) gender; (3) marital status; (4) number of children; (5) education level; (6) employment status; (7) household income.

### Planned Statistical Analysis of the Effects of the Intervention

#### Planned Preliminary Analysis

Descriptive statistics, correlation analysis, and attrition analysis (t-tests to compare the covariates and outcome variables of participants who drop out and those who complete the intervention) and randomization tests (one-way analysis of variance [ANOVA]) are conducted to test for differences in covariates and outcome variables between conditions using SPSS 28.

#### Planned Analysis of the Effects of the Intervention

The effects of the intervention on loneliness are assessed using mixed models for repeated measures. Specifically, a conditional growth model analysis with an unstructured covariance matrix is conducted using a Group (two intervention groups and one control group)  $\times$  Time (baseline, 4 weeks, and 3-, 6-, and 12-month follow-ups) interaction as an indicator of the intervention effects. For sensitivity analysis, a similar mixed model for repeated measures with an unstructured covariance matrix, but with the ANOVA model, is used. The demographic characteristics that show significant differences across groups at baseline are controlled for in the models. In addition, an “intention-to-treat” analysis is used to assess differences in outcomes by incorporating participants who do not complete the study. The intention-to-treat principle is also applied, and all statistical analyses are conducted using SPSS 28. In order to test the effect of the proposed mediators, path analyses with manifest variables will be run with indirect effect specified and tested with 95% bias-corrected confidence intervals resulting from 1000 bootstraps in Mplus 8. Mindfulness, happy/meaningful events, CRP, the position of candidate genes, polygenic risk scores and SNPs are potential mediators to be tested.

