## Supplement 1. Study Protocol

### Sample Size

A required sample size for the RCT on loneliness was estimated for one of the primary outcomes, that is, loneliness assessed by UCLA Loneliness Scale (54). A previous intervention study on reducing loneliness in older adults yielded an effect size of 0.5 (31). To be more conservative, we estimate the sample size based on a smaller effect size, i.e., 0.25. To detect an effect size of 0.25 at an alpha error rate of 0.05 and a power of 90%, the estimated sample size is 289 participants in each group. With an anticipated drop-out rate of 10% over a period of 6 months, the necessary sample size is 322 participants per group at baseline ( $N=966$  in total).

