### Study Design

Participants are interviewed by trained assessors using structured questionnaires at five time points: at baseline (pre-intervention) and at 4 weeks, 3 months, 6 months, and 12 months post-intervention. The baseline, 6-month, and 12-month follow-up assessments are conducted face-to-face, while the other two assessments are conducted over telephone. Because of the specific questions related to each intervention modality, volunteer callers cannot be blinded to the intervention modality, but they will be blinded to the study hypotheses. The intervention duration for the Tele-BA, Tele-MF, and Tele-BF groups is 4 weeks, with two sessions per week of approximately 30 minutes each (i.e., eight sessions in total). All intervention sessions are conducted by trained volunteers via telephone.

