### Volunteer Training and Training Materials

Tele-BA intervention was adapted from the Telehealth Behavioral Activation Treatment Manual for Homebound Older Adults (55). The Tele-MF intervention was adapted from the smartphone-delivered mindfulness intervention developed by Lindsay et al. (2019) to reduce loneliness in stressed adults (20). The Tele-BF active control condition was adapted from the BEFRIENDAS: Befrienders Information Guide by the National Ageing Research Institute (2020) (51). Each intervention includes eight sessions, with two sessions per week of approximately 30 minutes each, summing up to a four-week intervention period in total.

One experienced social worker and one research assistant are hired to deliver training sessions for Tele-BA, Tele-MF, and Tele-BF volunteers separately, making sure that the volunteers adhere to the respective intervention manual developed by the research team. Each volunteer is required to attend 6 weekly training sessions (2 hours per week) before they can independently conduct the intervention with older adults. A small group format, with four to six volunteers, is used to include role plays and practice in each session. The research

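### The models and the sample size ignore clustering by volunteer; if volunteers carry several participants and differ in their results, the intervals for the arm contrasts are too narrow

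*Protocol*

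**What the plan says.** On delivery, the Protocol (Study Design) says: "All intervention sessions are conducted by trained volunteers via telephone". Under Volunteer Training and Training Materials, one social worker and one research assistant "deliver training sessions for Tele-BA, Tele-MF, and Tele-BF volunteers separately". On format: "A small group format, with four to six volunteers, is used". Each volunteer attends six weekly sessions of two hours. Under Process Evaluation, participants rate their satisfaction with their own volunteer, which implies one identifiable caller per participant. Randomization is by individual and follows the baseline assessment.

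On analysis (Planned Analysis of the Effects of the Intervention): "The effects of the intervention on loneliness are assessed using mixed models for repeated measures". The main model is a conditional growth model with an unstructured covariance matrix, and Group x Time, with baseline among the time points, is the effect of interest. The sensitivity model keeps the same covariance structure with an ANOVA-type mean model. The only adjustment named is for demographic variables that differ between arms at baseline. Neither model has a term for volunteer or training group.

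On sample size (Sample Size), the target is a standardised effect of 0.25 with alpha 0.05 and 90% power, and the result reads: "the estimated sample size is 289 participants in each group". Allowing for 10% attrition over six months raises this to 322 per arm, 966 overall. No ICC or design effect enters. The Protocol does not give the number of volunteers or the caseload.

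**The concern.** Participants are randomised individually, but each arm is delivered by its own set of callers. If some volunteers get better results than others, participants who share a volunteer have correlated outcomes. The arm mean then carries a between-volunteer error that shrinks with the number of volunteers, not with the number of participants.

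This error arises after baseline, so it falls on the Group x Time contrast. Individual randomisation, baseline adjustment and the within-person covariance matrix do not remove it. A model that omits it counts differences between callers as evidence about the intervention. Its intervals are then too short, its type I error exceeds the nominal level, and real power is lower than an independence calculation suggests. Delivery by trained lay volunteers is also the Protocol's stated route to sustainability and scale, so the conclusions are meant to extend to other volunteers.

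**Working it through.** **1. The plan's own figure.** Inputs from Sample Size: d = 0.25, alpha 0.05, power 90%, 289 per group, dropout 10%. The sidedness is not stated; two-sided is assumed.
- n per arm = 2(1.960 + 1.282)²/0.25² = 336.2, so 337 (337.2 by the t distribution). One-sided it is 275. Neither gives 289.
- Two-sided at 85% power, the t calculation gives 288.3, so 289. Power with 289 per arm is 85.1%.
- The dropout step reproduces: 289/0.9 = 321.1, so 322; 322 x 3 = 966.

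The gap between 85% and 90% is a separate matter. It fixes the starting point here: any loss from clustering is counted from 85%.

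**2. Do participants share volunteers?** This is not stated. One volunteer per participant would need 966 volunteers. In training groups of 4 to 6 that is 966/6 = 161 to 966/4 = 242 groups. At 6 x 2 = 12 hours each, this is about 1,930 to 2,900 hours of training from two trainers. Sharing is therefore very likely.

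**3. Size, as an approximation for one follow-up comparison.** Assumed, because the Protocol gives neither: caseload m = 3 to 10, ICC = 0.01 to 0.05.
- Design effect DE = 1 + (m - 1) x ICC
- Effective n per arm = 289/DE
- Interval width should be multiplied by √DE
- Type I error if ignored = 2[1 - Φ(1.96/√DE)]
- Power from the two-sided two-sample t-test at 289/DE per arm, d = 0.25

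| m | ICC | DE | Effective n | √DE | Type I error | Power |
|---|---|---|---|---|---|---|
| any | 0 | 1.00 | 289 | 1.00 | 5.0% | 85.1% |
| 3 | 0.01 | 1.02 | 283 | 1.01 | 5.2% | 84.4% |
| 5 | 0.02 | 1.08 | 268 | 1.04 | 5.9% | 82.3% |
| 5 | 0.05 | 1.20 | 241 | 1.10 | 7.4% | 78.2% |
| 10 | 0.02 | 1.18 | 245 | 1.09 | 7.1% | 78.9% |
| 10 | 0.05 | 1.45 | 199 | 1.20 | 10.4% | 70.2% |

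The middle case (m = 5, ICC 0.05) costs 85.1 - 78.2 = 6.9 points of power. The low end costs 85.1 - 84.4 = 0.7 points.

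**4. Which volunteer term reaches the planned effect?** Illustration with assumed values: 58 volunteers x 5 participants = 290 per arm, baseline plus one follow-up, complete data, person variance 0.50, residual variance 0.45 per visit, volunteer variance 0.05. The person effect cancels from the change score, whose variance is 0.45 + 0.45 = 0.90.
- No volunteer variance: SE of the interaction = √(2 x 0.90/290) = 0.0788.
- Volunteer intercept constant over both visits: it enters baseline and follow-up alike and cancels, so the SE is again 0.0788. A generalised least squares calculation gives the same value.
- Volunteer effect at follow-up only: SE = √[2 x (0.90/290 + 0.05/58)] = 0.0891. A model without a volunteer term would take the change variance as 0.95 and report about √(2 x 0.95/290) = 0.0809.

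The interval is wrong only if volunteers affect change, and only a term that acts on change corrects it.

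**The case against.** **Caseload and ICC are assumptions.** This stands. A reader might infer that the intervals are certainly too narrow and the type I error certainly above 5%. The Protocol does not support that: with small caseloads or an ICC near 0 the effect is negligible. Some volunteer matters are referred to a separate protocol that is not at hand.

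**Not all of the power shortfall is clustering.** This stands. Reading the table against the stated 90% would suggest a 12-point loss in the middle case. About 5 points of that are present with no clustering at all.

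**The design effect is not computed for the planned estimator.** This stands as a caution. The formula suits one follow-up comparison. For Group x Time the relevant quantity is volunteer variance in change or slope, on which the Protocol has no figure.

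**Training groups.** A reader might infer that training groups are a source of correlation even with one participant per volunteer. The Protocol shows shared membership, not correlated outcomes, and it describes common manuals and shared slides intended to keep the groups comparable. That supports a sensitivity analysis and no more.

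**A provider term may be left to the SAP, and recruitment is closed.** This stands in part. An SAP could add the term, but the Protocol specifies both models without it, and the stated power would still assume independent participants. Restating power cannot change the enrolled number; it does change how a null or borderline result is read.

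**Conclusion.** The point holds conditionally. Volunteers are nested in arm, both stated models account only for repeated measures within a participant, and the sample size has no allowance for clustering. If volunteers carry several participants each and outcomes after baseline vary between volunteers, the intervals for the Group x Time contrasts are too narrow.

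The first condition is very likely from the Protocol's own training figures. The second is plausible but unquantified. Over the assumed range the consequence runs from negligible to a type I error about twice nominal. No single corrected sample size can be derived from the Protocol, and none should be asserted. The matter should be settled before the analysis is run, but it does not undermine the design.

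**What to change.** - **Models.** In the primary and sensitivity mixed models, add a volunteer random effect that acts on the post-baseline visits or on the slope (volunteer-by-time), or use robust standard errors clustered by volunteer. Do not rely on a volunteer intercept constant over all visits: it would leave the interval for the planned contrast essentially unchanged while appearing to deal with the problem.
- **Reporting.** Give the number of volunteers, the caseload and the volunteer ICC by arm.
- **Training group.** Use it as the cluster in a sensitivity analysis only.
- **Sample Size section.** State that the power assumes ICC = 0, and show it at 0.02 and 0.05 for the actual caseload.

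**Cost.** A volunteer identifier for each participant, one model term or a variance option, and a short power statement. No extra participants and no design change. The downside is somewhat wider intervals if volunteers differ.

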#### Participant Recruitment and Eligibility

This study protocol targets community-dwelling Chinese older adults. The inclusion criteria are as follows: (a) age 65 and older; (b) living alone; (c) living in poverty (i.e., monthly income < HKD 4,500 or USD 577); (d) able to communicate in Cantonese by telephone; (e) mild or no cognitive impairment; (f) no psychiatric disorder; (g) no Internet at home; (h) not engaged in regular mindfulness or a related mind-body practice; and (i) feeling lonely (score of 6 or higher on the three-item UCLA Loneliness Scale, Lin et al., 2020). Participants have been recruited through community centers for older adults, older-adult academies, and from public housing estates. The study's purpose, time commitment for participation, voluntariness, right to quit without negative consequences, and inclusion criteria have been clearly presented before a participant gives verbal consent to participate. Older adults who meet the above criteria have then been asked to sign a written informed consent form. The current stage of the study is that interventions and follow-up assessments are under way.

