### Randomization

After completing baseline assessment, participants are randomly assigned to either Tele-BA, Tele-MF, or Tele-BF using an online random number generated by a research assistant. Participants are then informed of their assigned intervention, and Tele-BA participants receive copies of BA worksheets. Due to the nature of the intervention, participants cannot be blinded as the types of activities in each intervention group are distinct.

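### Baseline loneliness enters the model only as a level of Time; a common baseline mean or a baseline covariate would give a more precise treatment contrast from the same data

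*Protocol*

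**What the plan says.** All references are to the protocol. Under Planned Analysis of the Effects of the Intervention, the primary model is named: "a conditional growth model analysis with an unstructured covariance matrix is conducted". The treatment effect is read from Group crossed with "Time (baseline, 4 weeks, and 3-, 6-, and 12-month follow-ups) interaction as an indicator of the intervention effects", so baseline loneliness is the first of five outcome occasions. The sensitivity analysis has the same structure: "a similar mixed model for repeated measures with an unstructured covariance matrix, but with the ANOVA model, is used".

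The only covariate rule is "The demographic characteristics that show significant differences across groups at baseline are controlled for in the models". Baseline loneliness is not a demographic characteristic, and it is not among the potential covariates listed under Demographic Information. Planned Preliminary Analysis does compare outcome variables between conditions, but only demographics are carried into the model.

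The Randomization section gives the order of events: "After completing baseline assessment, participants are randomly assigned to either Tele-BA, Tele-MF, or Tele-BF". Baseline loneliness is therefore measured before allocation.

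**The concern.** Because allocation follows the baseline measurement, any difference between arms in mean baseline loneliness is chance. A Group by Time model with its usual main effects does not use this. It estimates a separate baseline mean, or intercept, for each arm and subtracts it in full from the later difference, which adds baseline noise to the contrast. A model with one baseline mean for all arms, or with baseline as a covariate, subtracts only the part that baseline predicts.

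What is at stake is the width of the confidence intervals and the power for the two comparisons with befriending. Recruitment is reported as complete, so the analysis model is one of the few ways left to gain precision.

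**Working it through.** **Inputs.** From Sample Size: d = 0.25, alpha 0.05, 289 evaluable per group. From the analysis section: five occasions, three arms, unstructured covariance. Assumed, because the documents do not give them: ρ from 0.3 to 0.7, a two-sided test, and visit times for the linear case.

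**The plan's own figure.** The section states "To detect an effect size of 0.25 at an alpha error rate of 0.05 and a power of 90" percent and arrives at 289 per group. The dropout step reproduces: 289/0.90 = 321.1, rounded up to 322, and 3 × 322 = 966. The 289 does not. A two-sided two-sample calculation gives 337 per group at 90% power and a one-sided one gives 275; 289 matches a two-sided t-test at 85% power. That is a separate matter. Here 289 serves only as the sample size at which the two analyses are compared.

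**Categorical Time (the ANOVA-form model).** With complete data and a common SD, the variance of a two-arm contrast at one visit is (2·SD²/n) × k:
- Free baseline means: the contrast is a difference in change from baseline, k = 2(1−ρ).
- Common baseline mean, or baseline as covariate: k = 1−ρ².
- Ratio: (1−ρ²)/[2(1−ρ)] = (1+ρ)/2, never above 1.

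A generalised least squares check on a saturated three-arm, five-visit model, with and without a common baseline mean, gave the same ratios. The ratio applies visit by visit with that visit's own correlation with baseline, so the loss is larger at later visits if correlation decays.

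Power: d·√(n/2) = 0.25 × √(289/2) = 3.005, and power = Φ(3.005/√k − 1.96).

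| ρ | k, free | k, adjusted | Ratio | Power, free | Power, adjusted | n per arm for 90%, free / adjusted |
|---|---|---|---|---|---|---|
| 0.3 | 1.40 | 0.91 | 0.65 | 71.9% | 88.3% | 471 / 306 |
| 0.5 | 1.00 | 0.75 | 0.75 | 85.2% | 93.4% | 337 / 253 |
| 0.7 | 0.60 | 0.51 | 0.85 | 97.3% | 98.8% | 202 / 172 |

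At ρ = 0.8 the ratio is 0.90.

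**Linear Time (one reading of the growth model).** The contrast is now a difference in slopes. Take visit times of 0, 2, 4, 7 and 13 months (a four-week intervention, then follow-up counted from its end) and equal correlations ρ. The times sum to 26, their squares sum to 238, and the sum of squares about the mean is 238 − 26²/5 = 102.8.
- Free intercepts: the variance is proportional to (1−ρ)/102.8.
- Common intercept at time 0: the variance is proportional to (1−ρ)/[238 − 676ρ/(1+4ρ)], where 676 = 26².
- Ratio: 102.8/[238 − 676ρ/(1+4ρ)].

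At ρ = 0.3 this is 102.8/145.8 = 0.71; at 0.5, 102.8/125.3 = 0.82; at 0.7, 102.8/113.5 = 0.91.

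**The case against.** The strongest reply is that free baseline means are inferred. The protocol does not say whether a Group main effect is fitted, and such coding is commonly left to a SAP, which may exist. This stands as a condition on the point. If a common baseline is already intended, stating it settles the matter. But the protocol does fix the effect measure, the levels of Time and the covariate rule, and the default reading of those is free baseline means.

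Second, the primary model is a growth model. If Time is continuous there, the contrast is not a change-score difference, and the (1+ρ)/2 figures describe only the sensitivity model. This is correct. The loss in the linear case is smaller, 9% to 29% of variance over the same range of ρ, but in the same direction.

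Third, ρ is unknown and at high values little is gained. That also stands.

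A reader might infer two further things that the documents do not support:
- **That this loss explains why 289 per group gives about 85% rather than 90% power.** The 85% comes from a two-sample calculation that ignores baseline. The change score also gives 85% only at ρ = 0.5; at 0.7 it already gives 97%.
- **That the entry criterion, "feeling lonely (score of 6 or higher on the three-item UCLA Loneliness Scale", lowers ρ and so makes the planned contrast worse.** Selection can also work the other way. Take a follow-up-on-baseline slope of 0.5 and residual variance 0.75, and cut the baseline variance from 1 to 0.5. Follow-up variance is 0.25 × 0.5 + 0.75 = 0.875, and ρ falls from 0.50 to 0.38. Change-score variance is also 0.875, so the ratio is 0.75/0.875 = 0.86, a smaller penalty than the 0.75 before selection. Screening also uses the three-item scale, whereas the outcomes are the 20-item UCLA and the De Jong Gierveld scales. The documents do not settle which way the effect runs.

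**Conclusion.** The point holds as one of precision. On the default reading, the planned contrast has more variance than an analysis that uses the pre-randomisation loneliness score through a common mean or a covariate. With categorical Time, baseline adjustment removes 35%, 25% or 15% of the variance at ρ of 0.3, 0.5 or 0.7. With linear Time it removes about 29%, 18% or 9%. The categorical figures rest on complete data and equal SDs, the linear ones on equal correlations and assumed visit times, and all of them on an assumed ρ.

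A reader might infer that the planned estimate is biased by chance imbalance at baseline. It is not: under randomisation the contrast is valid, and the cost is a wider interval and lower power. The change is worth making because the data are already collected, but the result would not be invalid without it.

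**What to change.** State how Time is coded in the growth model and how baseline is handled in both models.
- **Growth model:** code Time as 0 at baseline, omit the Group main effect so that the arms share one baseline intercept, and keep Group by Time.
- **ANOVA-form model:** constrain the baseline means to be equal across arms and keep Group by post-baseline visit. Alternatively, model only the four follow-ups, with baseline loneliness and baseline-by-visit as covariates. The common-mean form keeps participants with no follow-up in the model, which sits more easily with the stated intention-to-treat aim.

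The section specifies this model for loneliness, and the change is proposed for that outcome. The cost is a small change of model specification and a dated note made before unblinded analysis. No further participants or measurements are needed.
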